**Discussion:**

The Run Clever trial will provide insight into possible differences in injury risk between running schedules emphasizing either running intensity or running volume. The risk of sustaining volume- and intensity-related injuries will be compared in the two intervention groups using a competing risks approach. The trial will hopefully result in a better understanding of the relationship between the running performed and possible differences in running-related injury risk and the injuries developed.

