Training errors are recognized as a risk factor for running-related injuries and in order to develop running schedules with a minimized risk of injury, a better understanding of the different training variables’ influence on injury risk is needed [14, 15]. Trials investigating differences in injury risk in relation to the progression in running volume, the frequency and duration of running and participation in a preconditioning programme, have been conducted [16–18]. The GRONORUN 1 and 2 trials both mentions the application of an subjective measure of running intensity as a limitation in the trials [19, 20]. The study by Pollock et al.[18] used maximal oxygen uptake as a relative measure of running intensity, comparing different durations of running and different weekly running frequencies. However, the sample consisted of male prison inmates between 20 and 35 years of age, which makes it difficult to generalize the results to recreational or novice runners. A review by Nielsen et al. concluded that there are moderate evidence suggesting that volume is associated with injury risk, but that this association possibly is influenced by the weekly progression in volume and the maturation of the runners [15]. The existing literature on running intensity and the development of injuries show conflicting results, possibly related to the subjective measure used in previous studies [15]. A possible association between the focus of a running schedule and the risk of sustaining specific injuries has also been hypothesized. Specifically, patellofemoral pain, illiotibial band syndrome and patellar tendinopathy were hypothesized to be distance-related, while achilles tendinopathy, gastrocnemius injury and plantar fasciitis were hypothesized to be pace-related [21]. Findings from both experimental and cohort studies support this hypothesized association. In an experimental study by Petersen et al. [22], an increase in running speed resulted in an increase in the peak plantar flexion moment, which was significantly higher than the increase in the peak knee extensor moment (*p* < 0.05). In another experimental study by Petersen et al. [23], a decreased running speed resulted in a cumulative load at the knee joint which was significantly higher, compared with the cumulative knee joint load at higher running speeds [22, 23]. An observational study by Nielsen et al. [24], with a 1-year follow-up and 847 novice runners included, investigated the progression in volume and found that greater progression in running volume increased the risk of the above mentioned distance-related injuries, but not the overall risk of injury. The aim of the Run Clever trial is therefore to conduct a training schedule intervention trial, comparing a running schedule which focus on running intensity with a running schedule which focus on running volume, with the purpose of extending the above mentioned studies, by investigating the difference in risk between the two training variables and the risk of sustaining specific injuries associated with a specific training variable. The following hypotheses are tested (H).Runners with a focus on running intensity have a 15 % increased risk of injury compared with runners with a focus on running volume.A running schedule focusing on intensity, increase the risk of sustaining achilles tendinopathy, gastrocnemius injuries and plantar fasciitis compared with hypothesized distance-related injuries.A running schedule focusing on running volume, increase the risk of sustaining patellofemoral pain syndrome, illiotibial band syndrome and patellar tendinopathy compared vwith hypothesized pace-related injuries.A positive excess risk due to interaction exists between running intensity and running volume, and the effect is more pronounced for pace-related injuries with greater changes in speed than volume, while the effect is more pronounced for distance-related injuries with greater changes in volume than in speed.

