### Statistical analysis

All data will be analyzed using an instrumental variable approach in the primary analysis [36]. The instrumental variable is the randomization. Secondary analyzes are intention-to-treat and per-protocol. Time to first injury is analyzed using the following primary time scale: calender time in days and weeks. Data will be analyzed at the following time-points: 2 weeks, 4 weeks, 8 weeks and 16 weeks after randomization. Secondary time scales are cumulative running volume in kilometres and cumulative running volume in minutes. Time of follow-up begins when the randomized interventions start. The unit of analysis is each participant. Participants will be right-censored in case of pregnancy, disease, lack of motivation, non-running-related injury causing a permanent stop of running, unwillingness to attend clinical examination in case of injury, if more than 10 % of all training sessions were uploaded manually (they will be censored at the time 10 % of uploads are manual) or at end of follow-up, whichever comes first.

The injury proportion as a function of the follow-up time scales mentioned above will be estimated using the Kaplan-Meier curve. The cumulative injury risk difference between groups is analyzed, performing a generalized linear regression, using the pseudo values method [37]. Competing risk analysis will be performed separately for both groups, to investigate difference in risk of hypothesized injuries including more than one endpoint [38]. The Aalen Johansen estimator will be applied in the competing risks analysis. Endpoints included in the competing risk analysis are non-running-related injury causing a permanent stop of running and the 20 injuries presented by Taunton et al. [13] In the intensity group (Sch-I) the risk of achilles tendinopathy, gastrocnemius injuries, and plantar fasciitis are analyzed in a competing risk model, treating the remaining 17 injuries as competing events. In the volume group (Sch-V) the risk of patellofemoral pain syndrome, iliotibial band syndrome, and patellar tendinopathy are analyzed in a competing risk model, treating the remaining 17 injuries as competing events [21]. Differences are considered statistically significant at *p* < .05, and estimates are presented with 95 % confidence intervals. All analyzes are performed using STATA/SE version 13 (or more if applicable).

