## Discussion

Run Clever is the first randomized trial to investigate how a running schedule focused on running intensity compared with a running schedule focused on running volume influences the overall risk of injury and the type of injuries sustained.

The population of interest is rapidly growing and should be prioritized, as it possibly is the largest group of recreational active adults worldwide [1, 41]. Recreational runners as a group are characterized by a large heterogeneity, especially concerning running experience and training habits. Consensus regarding the definition of a recreational runner is not established and the term is used inconsistently in relation to a wide variety of running populations. In three studies all describing the included runners as recreational, running experience in years ranged from 5.0 to 8.6 and the weekly volume in kilometers ranged from 28 to 38. However, the weekly running frequency only ranged from 3.0 to 3.8 [35, 42, 43]. The present trial defines the population as recreational runners, using the inclusion criteria of an average weekly frequency between 1 and 3 running sessions the past 6 months. The choice of weekly frequency was primarily based on a descriptive study by the Danish Institute for Sports Studies, which showed that the largest proportion of recreational runners in Denmark averaged 1 – 3 weekly running sessions [44].

The ideal percentage of weekly progression is unclear and a trial by Buist et al. comparing a weekly progression of 10.5 and 23.7 % found no difference in risk of RRI. However, a weekly progression of 30 % has been found to increase the risk of specific RRI [19, 24]. In an attempt to allow for adaptation to the progression in running, the research team developed the 4-week cycle, based on a theoretical step loading approach [29].

The follow-up Run Clever applies, aims at increasing the homogeneity of the included participants, in relation to the running performed most recently, prior to allocation to the intervention. Other running-related factors, such as running experience and previous running-related injury, are non-modifiable parts of the heterogeneity characterizing recreational runners, and can only be sought controlled for through the baseline data collection and complementary risk factor analysis.

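### The plan promises to compare the two schedules on type of injury, but it analyses each injury trio in one arm only, so no injury-type result can be attributed to the schedule

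*Protocol article*

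**What the plan says.** Two places describe a comparison between schedules. The Discussion paragraph of the abstract states: "The risk of sustaining volume- and intensity-related injuries will be compared in the two intervention groups using a competing risks approach". The main Discussion section says that the trial will show how one schedule, compared with the other, "influences the overall risk of injury and the type of injuries sustained".

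The hypotheses in the Background use a different comparator. H2 reads: "A running schedule focusing on intensity, increase the risk of sustaining achilles tendinopathy, gastrocnemius injuries and plantar fasciitis compared with hypothesized distance-related injuries". H3 is its mirror image for the three distance-related diagnoses under the volume schedule, "compared vwith hypothesized pace-related injuries".

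The Statistical analysis section then fixes the method: "Competing risk analysis will be performed separately for both groups, to investigate difference in risk of hypothesized injuries including more than one endpoint". The events differ by arm: "In the intensity group (Sch-I) the risk of achilles tendinopathy, gastrocnemius injuries, and plantar fasciitis are analyzed in a competing risk model", and "In the volume group (Sch-V) the risk of patellofemoral pain syndrome, iliotibial band syndrome, and patellar tendinopathy are analyzed in a competing risk model". In each arm the other 17 of 20 listed diagnoses are competing events, and the Aalen-Johansen estimator is used. The only between-group analysis written out is the pseudo-value regression for the cumulative risk of any injury.

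**The concern.** To say that a schedule raises the risk of an injury, one needs the risk of that injury under the other schedule. Here the pace-related trio is to be estimated only in Sch-I and the distance-related trio only in Sch-V. Setting the two results side by side would compare different events in different people. Setting one trio against the other within an arm would compare diagnoses in the same runners, and that comparison can come out unequal simply because some diagnoses are commoner than others.

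At stake is the trial's second main question. Randomisation offers a clean answer to it, and the analysis as written does not use randomisation for it.

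**Working it through.** **1. Can a between-arm contrast of injury type be formed from the stated analyses?**

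| Quantity | Sch-I | Sch-V |
|---|---|---|
| Any running-related injury | specified | specified, compared by pseudo-values |
| Pace-related trio | event of interest | not an event of interest |
| Distance-related trio | not an event of interest | event of interest |

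For each trio one cell is missing, so no contrast can be formed. The class-against-class contrast in H2 and H3 is not set up directly either: the opposite trio (3 diagnoses) is pooled with 17 − 3 = 14 others as competing events.

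**2. The plan's own figure.** The illustration uses the stated 620 participants before dropout, 310 per arm with equal allocation. Superiority by a 5-point margin, with 20 % v 35 % and unpooled variance, gives n per arm = (0.20×0.80 + 0.35×0.65) × (1.96 + 0.84)² / (0.15 − 0.05)², about 305, or 610 in total (626 with pooled variance). This is close to 620, which is not in dispute.

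**3. Within-arm contrast when the schedule has no effect.** Inputs: 310 per arm and two-sided 5 %. Assumptions, because the article gives no diagnosis-specific rates: overall risk 20-35 % and equal in both arms, the six diagnoses making up 40-60 % of injuries, no censoring. The test is also assumed, since the plan names none.

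With trio risks p1 (distance) and p2 (pace) in one arm:

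z = (p1 − p2) / √{[p1 + p2 − (p1 − p2)²] / 310}; P(significant, distance > pace) = Φ(z − 1.96).

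Examples at a frequency ratio of 1.5:
- Risk 20 %, share 40 %: p1 = 4.8 %, p2 = 3.2 %, z = 0.016/0.0160 = 1.00, P = 17 %.
- Risk 35 %, share 60 %: p1 = 12.6 %, p2 = 8.4 %, z = 0.042/0.0259 = 1.62, P = 37 %.

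Simulation (20,000 trials per setting) agrees:

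| Distance : pace frequency | Apparent support for H3 in Sch-V, no true effect |
|---|---|
| 1 | 2.5 % |
| 1.5 | 17-37 % |
| 2 | 39-78 % |
| 3 | 74-99 % |

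In Sch-I the same imbalance gives a significant result against H2 equally often. A between-arm test of either trio rejects in about 5 % of trials (both directions together) at every ratio.

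**4. Within-arm contrast when there is an effect.** Assume that pace-related injury truly doubles in Sch-I, from 4 % to 8 %, and distance-related injury is 8 % in both arms. The within-arm test then compares 8 % with 8 % and supports H2 in 2 % of trials. The between-arm test (8 % v 4 %) detects the effect in 57 %. If both trios start at 6 %, a doubling is found within arm in 72 % and between arms in 76 %.

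**5. Is a between-arm test of each trio enough?** Take the planned overall risks of 20 % and 35 % and assume that the mix of injuries is the same in both arms (30 % distance-related, 18 % pace-related).
- Distance trio: 6.0 % v 10.5 %; z = 0.045 / √[(0.06×0.94 + 0.105×0.895)/310] = 2.04; significant in about 53 % of trials, against H3.
- Pace trio: 3.6 % v 6.3 %; z = 0.027 / √[(0.036×0.964 + 0.063×0.937)/310] = 1.55; significant in about 34 %, in favour of H2.

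These are real differences in incidence, but they come from overall risk and not from a shift in type. The ratios show this: 10.5/6.0 = 1.75 and 6.3/3.6 = 1.75. The differences do not (4.5 v 2.7 points), so the contrast of the two arm effects should be on a ratio scale.

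**The case against.** **The analysis follows the hypotheses as written.** This is largely true. A reader might take H2 and H3 as between-arm claims because they speak of a schedule increasing a risk, but both name the other class of diagnosis as comparator. The fault is therefore not that the analysis departs from H2 and H3. It is that hypotheses and analysis together do not deliver what the abstract and Discussion announce.

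**The bias is not shown.** This also stands in part. A reader might infer that the common diagnoses win whatever the schedule does, so that H3 will be supported and H2 refuted. The article does not support that. It gives no diagnosis-specific rates, equal frequencies produce no bias, and a large effect can overcome an imbalance. The Background lists knee, lower leg and ankle/foot as the commonest sites. The last two are sites of the pace-related trio, so naming the knee first settles nothing.

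**No trio-versus-trio test is stated.** Correct. The percentages describe a test that a reader of H2 and H3 would naturally apply, not the error rate of a procedure in the plan.

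**The general analysis sentence covers it.** The section says: "All data will be analyzed using an instrumental variable approach in the primary analysis", with randomisation as the instrument. Within one arm the instrument is constant, so this cannot repair analyses that are expressly separated by arm. Whether the sentence was meant to govern them at all is a matter of interpretation, and nothing here depends on it.

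**A fuller plan may contain the comparison.** Possibly. But the article fixes arms, events, competing events and estimator, and what it fixes conflicts with its own abstract.

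**Conclusion.** The point stands on the text. The schedules are said to be compared on type of injury, yet neither trio is specified for estimation in both arms, so no finding on injury type from the stated analyses can be attributed to the schedule.

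The numerical consequence is conditional. Under assumed shares and an assumed test, false support for H3 ranges from the nominal 2.5 % with equally common classes to 39-78 % at a twofold imbalance, and the direction would reverse if pace-related injuries were the commoner class. A reader might also infer that the main result is compromised. It is not: overall injury has its own between-group pseudo-value analysis, which this point does not touch.

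**What to change.** - Reword H2 and H3 so that the other schedule is the comparator.
- Estimate the Aalen-Johansen cumulative incidence of both trios in both arms. Competing events are all other running-related injuries, including any outside the 20 listed, and non-running-related injury that permanently stops running. The same section also lists that last event as a reason for censoring, so it should be given one role in this analysis.
- Compare the 16-week cumulative incidence of each trio between arms as randomised, for example by pseudo-value regression, which is already planned for overall injury.
- Report the contrast of the two class-specific arm effects, preferably as a ratio of cumulative incidence ratios, to separate a shift in injury type from a difference in overall risk.
- Keep the within-arm curves as description, and state that the trial was not sized for these comparisons.

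The cost is a few sentences and a little code. No new data are needed, because reported running-related injuries in both arms are already referred to blinded physiotherapists who use the same diagnostic criteria.

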### Complementary risk factor analysis

To study if the effect of the intervention on the risk of RRI were modified by running experience, BMI, gender, previous injury, age and general activity level, a stratified analysis in accordance with the recommendations by Knol, *MJ* and Vanderweele, *TJ* [39] will be performed. All predictor variables will be included in the stratified analysis, provided that the recommendation of at least 10 injuries per predictor variable is fulfilled [40].

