
Furthermore, complementary risk factor analysis on BMI, age, gender, previous injury, running experience and general activity level will be performed. Of interest is the effect modification of the mentioned risk factors on the interventions’ influence on injury risk. Explorative analyzes will be performed on data collected using the Oslo Sports Trauma Research Center Questionnaire [25]. The focus of the explorative analyzes is the reported physical complaints progressing to time loss injuries and the relationship with the running performed.

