### Inclusion and exclusion criteria

Healthy persons who own an IOS- or Android-based smart-phone, between 18 and 65 years, with an average of 1 – 3 weekly running sessions the past 6 months are eligible for inclusion. Persons will be excluded if they have had an injury in the lower extremity 6 months preceding the baseline, or if any of the following contraindications for vigorous physical activity are present: Former heart or chest surgery, symptoms of chest pain, dizziness or discomfort when physically active, pregnant or taking prescribed medication related to cardiovascular problems, in accordance with the American College of Sports Medicine (ACSM) [27].

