#### Baseline measurements

Participants complete the baseline measurements through the online training diary. The baseline measurements are divided into four parts which are administered consecutively.is self-reported and covers personal information, demographics, medical history, information on running experience and the social security number. The self-reported height and weight will be used to calculate BMI (weight (kg)/height^2^ (m^2^)).covers current symptoms of overuse injury, using a modified version of the Oslo Sports Trauma Research Center questionnaire (OSTRC) developed by Clarsen et al. [25], to establish a baseline measurement of overuse symptoms.covers the baseline assessment of general physical activity during daily life. The Short Questionnaire to Assess Health-enhancing physical activity (SQUASH) is a tool, which assess habitual activity level during an ordinary week. Questions are pre-structured in four categories and information on days per week, average time and effort is collected. Time to complete the SQUASH questionnaire has been estimated to be 3 – 5 min [28].and final part of the baseline measurement, is a field-based self-administered physical performance test (PPT). The participants are required to download the Help2Run smart-phone application, to complete the self-administered physical performance test. Through the smart-phone application the participants select 1 out of 3 possible running tests: 6 min running test, Coopers 12 min running test or 5 km running test. When the preferred test is completed, the test results are used to prescribe the intensity of running for each of the participants.

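### Stratifying continuous effect modifiers (at least BMI and age) gives up information that a product term in the planned regression would keep; a minor, cheap improvement

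*Protocol article*

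**What the plan says.** The Background of the protocol article announces complementary risk factor analyses and adds: "Of interest is the effect modification of the mentioned risk factors" on how the interventions influence injury risk. The section Complementary risk factor analysis fixes the method. To see whether the effect on running-related injury is "modified by running experience, BMI, gender, previous injury, age and general activity level, a stratified analysis" will be done, following a cited recommendation. All six variables enter it, "provided that the recommendation of at least 10 injuries per predictor variable is fulfilled".

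How the variables are measured:

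- BMI: "The self-reported height and weight will be used to calculate BMI" (Baseline measurements).
- Age: eligible runners are "between 18 and 65 years, with an average of 1 – 3 weekly running sessions the past 6 months" (Inclusion and exclusion criteria).
- General activity: SQUASH, where "information on days per week, average time and effort is collected" (Baseline measurements). The final scoring is not stated.
- Running experience: the trial's own scale is not stated. For cited studies the Discussion reports that "running experience in years ranged from 5.0 to 8.6".
- Gender and previous injury are categorical.

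The section Statistical analysis makes an instrumental variable approach primary, with randomization as the instrument. It estimates the cumulative risk difference by "performing a generalized linear regression, using the pseudo values method".

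**The concern.** Strata treat everyone within a group as alike and discard the ordering inside it. For a modifier that acts gradually, this makes the estimate of modification less precise and dependent on where the cuts fall. The article already plans a regression on the risk-difference scale that could carry a continuous modifier without new data.

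What is at stake is the chance of seeing real modification by BMI, age, experience or activity. The Discussion describes recreational runners as very heterogeneous, notably in experience, and relies on the baseline data and this complementary analysis to deal with that.

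**Working it through.** **Inputs.** From the section Power: injury risk 20 % (volume) and 35 % (intensity), 620 runners before loss, 15 % loss, 713 in total. From Randomization: equal groups. From Statistical analysis: 5 % significance, taken here as two-sided. From the Discussion: a minimum acceptable 357. Assumptions of this check, not in the article: the distribution of the modifier, a linear interaction and its size.

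**The plan's own figure.** The article gives no figure for effect modification. Its 620 is nearly reproduced as superiority by a 5-point margin: [0.20×0.80 + 0.35×0.65] × (1.960 + 0.842)² / (0.15 − 0.05)² = 304.1, so 305 per arm and 610 in total. The planning risks are therefore usable here. The analysed number is taken as 713 × 0.85 = 606, or 303 per arm.

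**Information kept by strata.** For a linear interaction, the share kept is Var(E[X | stratum]) / Var(X). For a normal X cut at the median this is 2/π = 0.637. The share lost is:

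| Modifier | 2 strata | 3 | 4 | 5 |
|---|---|---|---|---|
| Normal, equal-sized strata | 36 % | 21 % | 14 % | 10 % |
| Uniform, equal-sized strata | 25 % | 11 % | 6 % | 4 % |
| Lognormal (sigma 0.8), equal-sized strata | 63 % | 48 % | 40 % | 35 % |

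A two-way cut of a normal modifier loses 42 % at 30/70 and 51 % at 20/80.

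**Precision at 606.**

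- Main risk difference: SE = √[(0.16 + 0.2275)/303] = 3.58 points.
- Difference between two equal strata: SE = 2 × 3.58 = 7.15 points. The 95 % interval is about ±14 points, and about 20 points is detectable with 80 % power (2.80 × 7.15).
- Slope per SD with the modifier continuous: SE about 3.58 points, since the modifier then has variance 1.

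**Power for an assumed 10 points per SD.**

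- Continuous: z = 10/3.58 = 2.80; power = Φ(2.80 − 1.96) ≈ 80 %.
- Median split: the halves differ by 2 × √(2/π) = 1.596 SD, so the contrast is 15.96 points; z = 15.96/7.15 = 2.23; power ≈ 61 %.
- Tertiles, tested as a trend: z = 2.80 × √0.793 = 2.49; power ≈ 70 %.

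Simulation with a linear probability model and robust standard errors agrees: 81 % v 61 % at 606 and 82 % v 62 % at 620. With no interaction, rejection at 606 was 5.2 % continuous and 4.8 % split.

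**Other settings, continuous v median split.**

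- 8 points per SD at 606: 63 % v 43 % (simulation).
- 5 points per SD at 606: z = 1.40 v 1.12, so about 29 % v 20 %.
- 10 points per SD at the minimum size (357 × 0.85 = 303 analysed): SE = √(0.3875/151.5) = 5.06 points; about 51 % v 35 %.

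**The case against.** The strongest reply is that the size of the loss is not in the article. A reader might infer that about a third of the information will be thrown away. That needs two strata, a median cut, a normal modifier and a linear interaction. The article states none of these, and the number of strata and the cut-points may properly sit in an analysis plan that is not shown. This stands: only the range can be given.

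Other parts of the reply also stand:

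- Continuity is clear for BMI and age only. For running experience and activity it is an inference.
- The article neither mentions nor excludes a product term. Its rule on injuries per variable could suggest a model behind the strata, and the cited recommendation is not available here. It would be wrong to say that strata are the only analysis intended.
- A reader might add the loss from cutting to the doubled standard error of a subgroup contrast. That counts it twice, because the doubling belongs to the two-strata contrast. The continuous slope per SD has about the main-effect standard error.
- A linear interaction is the case most favourable to a product term. If the effect steps at the median, a linear term loses the same 36 %. If it is symmetrically U-shaped, a linear term finds nothing, while three or more strata could.
- Ten points per SD is strong modification: around a mean difference of 15 points it runs from −5 at −2 SD to +35 at +2 SD.

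The reply does not remove the direction of the point. Stratification is the method the article states for all six variables. For gradual modification every grouping loses something, and pre-set cut-points would limit analyst freedom without recovering it.

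**Conclusion.** The point holds as a modest gain in efficiency. If modification is roughly linear, stratifying a continuous modifier costs about 36 % of the information (median split, normal modifier), 21 % (tertiles) or 10–14 % (four or five groups). The cost is higher for skewed variables or off-centre cuts and lower for a flat distribution. The 80 % v 61 % comparison illustrates an assumed strong interaction; it does not predict this trial's power. For weaker interactions, or at the minimum sample size, neither method answers the question well.

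A reader might conclude that the planned analysis is invalid. The article does not support that: the median split holds its 5 % error rate, and stratum-specific risks are a legitimate description. The analysis is complementary, is not among the four listed hypotheses and did not set the sample size, so the point is minor.

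**What to change.** State that effect modification by BMI and age, and by running experience and the activity score if these are recorded on a quantitative scale, will be estimated with an arm-by-modifier product term, modifier continuous, in the pseudo-value regression for the risk difference. In the instrumental variable version, add randomization-by-modifier as the instrument for the product term. Fit a spline as a check on linearity. Stratify gender and previous injury, and show strata of the continuous variables for presentation only.

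The cost is a short addition to the analysis text and no new data. Fitted one modifier at a time, the linear model has three terms (arm, modifier, product). Read as 10 injuries per term, the article's rule would ask for 30, against about 303 × (0.20 + 0.35) = 167 expected. The downsides are the approximate-linearity assumption and some loss of power where the spline is needed.
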